relationship in which the lowest group (underweight and abstainers) has increased risk compared to those in the moderate categories. Reverse causality by unmeasured health problems may explain this pattern in these groups. In a Swedish intergenerational study, offspring BMI was used as an instrumental variable for own BMI as BMI in the offspring is less likely to be affected by health problems. The authors found less adverse consequences of lower BMI compared to conventional observational studies. Alcohol consumption in family members can be used similarly as instrument for own consumption to avoid the problem of sick quitters potentially producing non-causal increased risk compared to moderate drinkers (RQ 3). In both cases offspring alcohol and BMI are recorded earlier in life whereas CVD in parents is recorded at a higher age. More generally, using family proxies for exposure might be valuable not only to reduce reversed causality, but also because their alcohol intake will be less strongly associated with the individuals' other risk factors that predisposes him/her for CVD, i.e smoking and diet, and give less biased estimates of effect than own alcohol exposure.

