### **Data sources**

The Cohort of Norway (CONOR) Data from 10 epidemiological studies (n=181,891) from 1994-2003 have been merged into a national database. All the surveys included self-reported health and selected diseases, various risk factors, socio-demographic factors, use of medications and physiological measures such as blood pressure, cholesterol, triglycerides, waist and hip circumference, height and weight.

The Norwegian Twin Registry (NTR) Panel II were born 1915-1960. Questionnaires on alcohol consumption were sent out in 1980 and 1990 and 14 500 responded to one of these. These questionnaires included detailed reports on health and risk factors.

Norwegian Family Based Life course Study Data from all 7,400 000 Norwegian citizens alive between 1960 to 2010 has been linked to family data and several health surveys and registers. Family linkage is available for more than 90 % of those born after 1940. This is linked to several other cardiovascular health surveys in addition to CONOR (in total 730,000) and the Conscript Registry.

Hospital discharges on cardiovascular diseases in Norway (FS-data): Data on all cardiovascular hospitalizations in Norway between 1994 and 2009 has been obtained through patient administrative systems at Norwegian hospitals. This includes coronary heart disease (both myocardial infarction and unstable angina), stroke and atrial fibrillation.

Social security registry (FD-trygd): Data on disability pension, sickness and social security benefits on all Norwegian citizens from 1992 onwards. Diagnosis will be ICD-10: F01-F99 (Mental, behavioral and neurodevelopmental disorders)

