### **Samples (sub-populations)**

#### **RQ 1:**

The CONOR and the NTR will be pooled together and the NTR will be used as a cohort for this purpose. This will include n=47,848 from CONOR and n=8028 individuals from NTR (n=55,876 in total) with complete data on both moderate and binge drinking. Mean year of birth is 1947 in CONOR and 1941 in the NTR sample. More deaths occur in the NTR (n=1453 deaths) compared to CONOR (n=1805 deaths). Number of CVD deaths in the CONOR sample with follow-up until 2010 is 547. Based on the proportion of CVD mortality and all-cause mortality and number of fatal and non-fatal cases in the FS-database, total

number of cases, including both CONOR and the NTR is expected to be 3000 IHD and 3500 cases of stroke.

RQs 2 and 3:

This will include the CONOR and twin populations linked to the FS-data on hospital discharges, the Cause of Death Registry, the Conscript Registry (cognitive ability) and Social Security Registry (mental health problems). Two separate sub-populations of CONOR will be studied: all subjects who responded to items on moderate alcohol consumption (n=162,048) and, nested in this sample, those who responded to items on both moderate and binge drinking (n=47,848). In the first group there are 3774 deaths from CVD. There are in total 9735 acute myocardial infarction and 8926 stroke incident cases from the FS-database in CONOR. For the second group, see RQ1.

RQ 4:

This issue will be analyzed in a linkage between CONOR, cardiovascular health surveys in the Norwegian Family Based Life course study and the FS-data on hospital discharges. There are 116,037 individuals in CONOR with information on parents and siblings. Of these, 109,800 individuals have responded on the moderate alcohol consumption question with 9729 CVD deaths in fathers and 31,050 on the binge drinking question with 1854 CVD deaths occurring after the year of CONOR examination.

RQ 5:

CONOR: There are 48,401 siblings in CONOR with the same mother and father. 1025 of these have by 2010 died (281 CVD). We expect approximately 1400 CVD endpoints in the FS-database. For the second group on siblings, see RQ 1.

RQ 6:

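### RQ 4: recording offspring drinking earlier in life than parental CVD does not establish that the family instrument avoids sick-quitter bias; it may reduce it, and the plan should say so and test it

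*Protocol*

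**What the plan says.** The section on approaches, hypothesis and choice of method proposes alcohol consumption in family members as an instrument for own consumption, "to avoid the problem of sick quitters potentially producing non-causal increased risk compared to moderate drinkers". It borrows the reasoning of an intergenerational BMI study, in which "BMI in the offspring is less likely to be affected by health problems", and adds: "In both cases offspring alcohol and BMI are recorded earlier in life whereas CVD in parents is recorded at a higher age". That section labels this work RQ 3; the list of research questions and the statistical methods call it RQ 4, the label used here. The list names both siblings and offspring as instruments.

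Under Samples, RQ 4, the exposure comes from CONOR participants: "109,800 individuals have responded on the moderate alcohol consumption question with 9729 CVD deaths in fathers". The smaller sample, which also answered the binge item, is given as "31,050 on the binge drinking question with 1854 CVD deaths occurring after the year of CONOR examination". CONOR is described as "Data from 10 epidemiological studies (n=181,891) from 1994-2003". Its frequency item covers the last year, and the lowest recoded category is Never/seldom. For the RQ 1 sample, "Mean year of birth is 1947 in CONOR and 1941 in the NTR sample".

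The data analysis paragraph says RQ 4 is meant to show whether the instrument reproduces the protective effect seen conventionally. It lists self-reported CVD, diabetes and antihypertensive medication at baseline among the adjustment variables. The section on relevance to the call says that both drinking and CVD risk cluster within families.

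**The concern.** Sick quitting can bias an analysis whenever drinking is reported after illness has had time to change it. Being younger than one's father does not mean reporting before that can happen. CONOR offspring are adults describing the past year, and some may already have cut down or stopped because of illness. They then sit in the lowest category with people who never drank.

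For this to matter in the father's analysis, the offspring's illness must be related to the father's CVD. The protocol supplies that link when it says CVD risk clusters in families. For sibling instruments the timing argument does not apply, because a sibling belongs to the index person's own generation.

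RQ 4 asks whether a protective pattern reappears when relatives' drinking is used. Residual sick quitting pushes towards a yes. If the instrument is described as avoiding the bias, a reappearing pattern will carry more weight than it has earned.

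**Working it through.** **1. Age when drinking was recorded.** Survey years 1994-2003 (Data sources) and mean birth year 1947 (Samples, RQ 1): 1994 - 1947 = 47 and 2003 - 1947 = 56. The 1947 figure describes the RQ 1 sample (n=47,848); none is given for RQ 4. The RQ 4 subset is 116,037 of 181,891 participants (64%), and "Family linkage is available for more than 90 % of those born after 1940", so it may be younger.

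**2. The only RQ 4 effect estimate.** The sample size paragraph gives a hazard ratio for CVD death in fathers, abstaining against moderate-drinking offspring, of 0.93 (0.88-0.99). It comes from data and cannot be re-derived, but its consistency can be checked:
- Geometric mean of the limits: √(0.88 × 0.99) = 0.933.
- Standard error: ln(0.99/0.88) / (2 × 1.96) = 0.030.
- Using variance 1/(d·p(1-p)), d = 9729 deaths gives p(1-p) = 0.114, so about 13% abstainers. With d = 1854, p(1-p) would be 0.60, above the maximum of 0.25. The estimate therefore fits the larger sample.
- The text calls the risk higher among abstainers, but 0.93 is lower. Inverted, it would be 1.08 (1.01-1.14).

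**3. Simple illustration of carry-over (assumed inputs).** Let 15-25% of abstaining offspring have quit through illness, let their fathers' CVD hazard be 1.3-1.5 times that of others, and let alcohol have no effect. With no ill offspring in the comparison group, the ratio is 1 + share × (ratio - 1):
- 1 + 0.15 × 0.3 = 1.045
- 1 + 0.25 × 0.5 = 1.125

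If 10% of the moderate drinkers are also ill, the ratios fall to 1.045/1.03 = 1.01 and 1.125/1.05 = 1.07.

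**4. Simulation of carry-over (assumed inputs).** Four million father-offspring pairs per scenario, with no alcohol effect. Illness is the upper tail of a normal liability: 5-20% of offspring are ill, 30-50% of the ill and 10% of the well abstain, and father CVD death is set at 9% (9729/109,800 = 8.9%). The offspring's own later event has correlation 0.6 with the liability.

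| Father-offspring liability correlation | Spurious risk ratio in fathers, abstaining vs other offspring |
|---|---|
| 0 | 1.00 (0.995-1.009) |
| 0.1 | 1.05-1.15 |
| 0.25 | 1.12-1.41 |
| 0.5 | 1.33-2.05 |

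The ratio for the offspring's own outcome was 1.42-2.40, above the fathers' ratio in every scenario. That ordering follows from setting every familial correlation below 0.6. Abstaining is random within the ill and within the well here, so adjustment for perfectly measured illness would remove the carry-over. What survives in practice is illness the adjustment variables miss.

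**5. Order of events.** The condition that death follows the examination is attached to the 1854 deaths; whether it also covers the 9729 is unclear. Counting only later deaths limits the analysis to fathers alive at that date. If fathers are 25-35 years older (assumed), their average age then would be about 47 + 25 = 72 to 56 + 35 = 91.

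**The case against.** Much of the defence stands. The timing sentence is true as a comparison of offspring with their parents. The same section also speaks of BMI being less likely to be affected and of reducing reversed causality, so the protocol does not consistently claim complete protection. It also plans adjustment for baseline CVD, diabetes and antihypertensive medication. What remains is that *avoid* is the stated purpose. The adjustment paragraph does not say whose baseline values enter RQ 4, and adjustment cannot reach the unmeasured health problems that the protocol itself names as a possible cause.

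Four stronger readings are tempting and are not supported:
- *The fault would exist even without shared family factors.* It would not: at zero familial correlation the simulated ratio is 1.00. This is shared familial risk, not a separate timing error.
- *Offspring drinking is no better than own drinking.* The documents do not show this. If the familial correlation is weaker than the link between a person's illness and their own later CVD, the proxy reduces the bias.
- *The hazard ratio of 0.93 shows the bias at work.* As printed it runs opposite to a sick-quitter artefact, and the accompanying text contradicts it. Until that is resolved it supports neither side.
- *Offspring are known to be middle-aged and fathers 72-91.* The first borrows the RQ 1 birth year and the second adds an assumed generation gap.

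Time scale and delayed entry are details commonly left to the analysis plan and are not criticised here.

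**Conclusion.** The point holds in a limited form. Timing alone does not secure the property claimed for the family instrument: the report is an adult's last-year answer that groups quitters with never-drinkers, and siblings gain nothing from the timing argument. Residual bias through familial illness remains possible and points towards the protective pattern RQ 4 is looking for. It is probably smaller than with own exposure.

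Its size cannot be fixed from the documents. It ranges from nil at zero familial correlation to roughly 5-15% at a correlation of 0.1 and 12-41% at 0.25, before adjustment and on assumed shares of illness and quitting. The simple illustration gives 1-13%. RQ 4 remains worth running; what needs correcting is the strength of the claim and the lack of a check on it.

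**What to change.** - In the section on approaches, hypothesis and choice of method, replace *avoid* with *reduce* where sick quitters are discussed. The sentence comparing offspring and parental timing can stay.
- Alongside the main RQ 4 analysis, report one sensitivity analysis with the exposure taken only from offspring and siblings without self-reported CVD, diabetes or antihypertensive medication at CONOR. Report another limited to younger respondents, with the age limit chosen by the sponsor in advance.
- Count only parental CVD events after the offspring's examination, in both the 109,800 and the 31,050 samples, and state that the results apply to parents alive at that date.

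The protocol lists self-reported disease and medication among the items CONOR collected, so no new data are needed. The cost is fewer events and wider intervals in the restricted analyses. If the 9729 deaths include some before the examination, the main analysis loses those too.

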### **Data sources**

The Cohort of Norway (CONOR) Data from 10 epidemiological studies (n=181,891) from 1994-2003 have been merged into a national database. All the surveys included self-reported health and selected diseases, various risk factors, socio-demographic factors, use of medications and physiological measures such as blood pressure, cholesterol, triglycerides, waist and hip circumference, height and weight.

The Norwegian Twin Registry (NTR) Panel II were born 1915-1960. Questionnaires on alcohol consumption were sent out in 1980 and 1990 and 14 500 responded to one of these. These questionnaires included detailed reports on health and risk factors.

Norwegian Family Based Life course Study Data from all 7,400 000 Norwegian citizens alive between 1960 to 2010 has been linked to family data and several health surveys and registers. Family linkage is available for more than 90 % of those born after 1940. This is linked to several other cardiovascular health surveys in addition to CONOR (in total 730,000) and the Conscript Registry.

Hospital discharges on cardiovascular diseases in Norway (FS-data): Data on all cardiovascular hospitalizations in Norway between 1994 and 2009 has been obtained through patient administrative systems at Norwegian hospitals. This includes coronary heart disease (both myocardial infarction and unstable angina), stroke and atrial fibrillation.

Social security registry (FD-trygd): Data on disability pension, sickness and social security benefits on all Norwegian citizens from 1992 onwards. Diagnosis will be ICD-10: F01-F99 (Mental, behavioral and neurodevelopmental disorders)

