## 1. Relevance to the call for proposals:

The health effect of alcohol consumption pattern (moderate and binge drinking) is of significant public health relevance because alcohol consumption in Norway and other countries in Northern Europe have been increasing since 2000. Furthermore, the consumption pattern is changing from binge drinking towards moderate regular intake. Norway is in a fortunate position to address this issue because large scale health surveys with data on both moderate and binge drinking have been linked to a multigenerational database, hospital discharge on CVD morbidity and mortality and other registries.

The national policy building upon a premise that total consumption affects number of problem drinkers might be under pressure. An implication of this principle of solidarity is that anyone can potentially experience health problems due to alcohol consumption. However, the scientific evidence base for population wide approaches is challenged for several reasons:

First, the effect of alcohol consumption on CVD appears to be divergent (RQ 1). But also, alcohol consumption might be influenced by underlying factors, which calls for a reconsidering on the issue of human agency in policy formulation. Individual and personal characteristics, such as psychosocial and cognitive, might explain a large and increasing part of the variation in health behavior (RQ 2). It has also been suggested that personal characteristics to an increasing extent explain socioeconomic inequalities in health. A better understanding of vulnerable subgroups in modern society where according to social theorists, the individual is put at an increased responsibility for managing their own health risk, is imperative for developing future health and alcohol policy. And finally, both alcohol consumption and CVD risk tend to be clustered within families (RQ 3&4). This could indicate the scope for early prevention of both harmful alcohol use and CVD.

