Data analysis: For time to event outcomes such as morbidity and mortality the primary modelling strategy is to use Cox proportion hazard regression models. In RQ 1 the effect of moderate alcohol consumption will be analysed by adjusting for binge drinking and across strata of binge drinking (interaction term will be fitted to formally test if the effect differs). In RQ 2-3 the same strategy will be employed using strata of cognitive ability and mental health. In RQ 4 the aim is to see if using alcohol consumption among family members as instrumental variable will reproduce a protective effect of moderate alcohol consumption as seen in conventional analysis. Using instruments, it will also be possible to estimate the effect sizes and compare the effect and pattern in CONOR participants with that of their sibling. To achieve this, z-scores will be calculated based on units of alcohol consumption reported. For RQ 5, the effects of alcohol consumption will be estimated by comparison between siblings or co-twins ("fixed effect"). This approach effectively matches out all factors shared between siblings that may confound the effect of alcohol on cardiovascular mortality reported in studies of unrelated individuals. The analyses will be conducted in the statistical software STATA. Age, smoking status and number of cigarettes per day in smokers, physical activity, self-reported disease (CVD, diabetes, antihypertensive medication) and psychosocial distress at baseline will be adjusted for as potential confounders. In

familial aggregation analysis, we will estimate to what extent alcohol related mortality co-occur in first degree family members with CVD morbidity and mortality and mental distress by summing up number of family members with any of these traits.

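### The stated adjustment set and strata for the conventional Cox models in RQ 1-3 leave out survey, although CONOR merges ten surveys from 1994-2003; stratifying by survey would guard against possible confounding of unknown size and direction.

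*Protocol*

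**What the plan says.** - **Data.** Protocol, Data sources, on CONOR: "Data from 10 epidemiological studies (n=181,891) from 1994-2003 have been merged into a national database". For RQ 1 these data are pooled with 8,028 twins from the NTR, whose alcohol questionnaires date from 1980 and 1990.
- **Time trend in the exposure.** Protocol, section 1 (Relevance to the call): "alcohol consumption in Norway and other countries in Northern Europe have been increasing since 2000", and "the consumption pattern is changing from binge drinking towards moderate regular intake".
- **Model.** Protocol, Statistical methods, for time-to-event outcomes: "the primary modelling strategy is to use Cox proportion hazard regression models". No time scale is given.
- **Adjustment.** The potential confounders named are "Age, smoking status and number of cigarettes per day in smokers, physical activity, self-reported disease (CVD, diabetes, antihypertensive medication) and psychosocial distress at baseline".
- **Strata.** "In RQ 1 the effect of moderate alcohol consumption will be analysed by adjusting for binge drinking and across strata of binge drinking". Then "In RQ 2-3 the same strategy will be employed using strata of cognitive ability and mental health".

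Survey, place and year of examination appear neither as covariates nor as strata of the baseline hazard.

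**The concern.** The protocol itself says that both dimensions of its exposure move with calendar time, and it then merges surveys taken over a decade. Survey is the variable that would carry such a shift, together with any difference in place. Adjusting for age does not stand in for it: a 50-year-old examined in 1994 and a 50-year-old examined in 2003 get the same covariate value and the same baseline hazard, yet belong to different surveys and are followed through different calendar years.

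If surveys with more regular drinkers also had a lower CVD hazard after adjustment, part of that difference would be credited to regular drinking. If they had a higher hazard, a real benefit would be masked. The study is meant to separate a true protective effect of moderate drinking from artefact, and its large samples make even a bias of a few per cent relevant in the models with most events.

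**Working it through.** **No figure to reproduce.** The protocol states no number on this point, and no survey-specific drinking prevalences or CVD rates. What follows is an illustration with assumed inputs.

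**Formula.** Collapse the surveys into an early and a late group. Let s be the share of participants in late surveys, e1 and e0 the prevalence of regular drinking in late and early surveys, and h the late-to-early CVD hazard ratio given the adjusters. Then

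- P(late | drinker) = s·e1 / [s·e1 + (1−s)·e0]
- P(late | non-drinker) = s(1−e1) / [s(1−e1) + (1−s)(1−e0)]
- apparent HR when the true HR is 1 = [1 − P(late | drinker)(1−h)] / [1 − P(late | non-drinker)(1−h)]

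**Assumed cases.**

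| s | e1 vs e0 | h | P(late, drinker) | P(late, non-drinker) | apparent HR |
|---|---|---|---|---|---|
| 0.3 | 0.30 vs 0.25 | 0.9 | 0.090/0.265 = 0.340 | 0.210/0.735 = 0.286 | 0.9660/0.9714 = 0.994 |
| 0.4 | 0.40 vs 0.25 | 0.8 | 0.160/0.310 = 0.516 | 0.240/0.690 = 0.348 | 0.8968/0.9304 = 0.964 |
| 0.5 | 0.40 vs 0.25 | 0.7 | 0.200/0.325 = 0.615 | 0.300/0.675 = 0.444 | 0.8154/0.8667 = 0.941 |

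If e1 = e0 or h = 1, the apparent HR is exactly 1.000.

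**Direction.** Keep the middle row but reverse the hazard difference, h = 1/0.8 = 1.25. The result is (1 + 0.516×0.25)/(1 + 0.348×0.25) = 1.129/1.087 = 1.039. Since place as well as year separates the surveys, either sign is possible.

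**Scale against the planned effect.** The protocol assumes a relative risk of 0.75 for average consumption. The extreme row amounts to ln(0.941)/ln(0.75) = 0.21 of that on the log scale. If calendar time alone had to produce h = 0.7, with the centres of the two halves of 1994-2003 about 4.5 years apart, the yearly fall in adjusted hazard would be 1 − 0.7^(1/4.5) = 7.6%. The protocol gives no such trend.

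**Scale against sampling error.** With an exposed share of about 0.30, the standard error of the log HR is at least about 1/√(events × 0.3 × 0.7).

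- Using the 9,735 myocardial infarctions reported for CONOR: 1/√(9,735 × 0.21) = 0.022. The three rows are then about 0.3, 1.7 and 2.8 standard errors.
- Using the 547 CONOR CVD deaths in the RQ 1 sample: 1/√(547 × 0.21) = 0.093. Even the extreme row is then 0.061/0.093 = 0.65 standard errors.

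**Binge data.** 47,848 of the 162,048 CONOR participants with the moderate-drinking item (29.5%) also have the binge item. The protocol does not say which surveys these come from, so no comparable calculation is possible for the binge hazard ratio.

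**The case against.** The strongest reply is that one sentence of potential confounders in a protocol is not a closed list. It omits sex, although the protocol reports more frequent binge drinking in men, and it omits education, which RQ 3 studies. The time scale and the mechanics of pooling are also left open, and an analysis plan that is not at hand may add survey. It is true that the list may be incomplete. But the protocol does state its adjustment set and its strata for these models, and as stated they do not separate the surveys.

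The second reply is that the protocol does not show confounding. This stands. Consumption rising since 2000 covers only the end of the survey window. The shift away from binge drinking is cited to a report whose title spans 1973-2004. Neither statement says that drinking differed between the CONOR surveys, and nothing is said about CVD rates by survey.

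A reader might therefore infer more than the document supports:

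- **That survey differences do enter the hazard ratios and create a spurious protective effect.** Both links are needed, neither is documented, and the sign is open.
- **That unequal follow-up is itself a fault.** With hospital data ending in 2009, follow-up runs from about 15 years for the first surveys to about 6 for the last. A Cox model handles this through its risk sets; only a difference in hazard between surveys would bias it.
- **That the binge effect is pushed in the harmful direction.** If few surveys supplied the binge item, there may be little contrast between surveys to cause any bias.
- **That one fifth of the assumed effect is at risk.** That is the extreme corner of assumed inputs, not an estimate.

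**Conclusion.** The point holds as a modest improvement to the specification, not as a demonstrated bias. As written, the conventional CONOR models in RQ 1-3 compare drinkers across ten surveys while the protocol itself describes a changing exposure. Confounding by survey is plausible, and it needs both drinking and the adjusted CVD hazard to differ between surveys.

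Under the assumptions tabulated above, a true null would appear as about 0.94-0.99. With the opposite hazard difference it would lie above 1, and with either link absent it stays at 1.00. A shift towards the upper end of that range would matter in the models with thousands of events and would be lost in the noise of the model with 547 deaths.

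The point concerns the surveys inside CONOR, so a single CONOR-versus-NTR term would not settle it. The within-family comparisons of RQ 5 are not part of it.

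**What to change.** In the data-analysis paragraph of Statistical methods, state that the conventional Cox models in RQ 1-3 stratify the baseline hazard by contributing CONOR survey, using as many strata as there are surveys that supply the exposure in question, with NTR as its own stratum wherever it is pooled. Name the surveys that supplied the binge item, so that the number of strata in the binge models is known.

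The cost is one option in the Cox command and some precision. A rough gauge is the share of exposure variance that lies between surveys. In the middle assumed case this is 0.4 × 0.6 × 0.15² / (0.31 × 0.69) = 0.0054/0.2139 = 2.5%, so the standard error rises by a factor of 1/√(1 − 0.025) = 1.013. Larger prevalence differences across the actual surveys would raise this, and the loss is felt most in models with few events, such as the 547 CONOR CVD deaths in RQ 1. If the surveys do not differ, the hazard ratios will barely change.

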## **2. Aspects relating to the research project**

### **Background and status of knowledge**

Alcohol has a negative effect on many health-related outcomes but for heart diseases the effects seem to be mixed. Alcohol use is negatively related to hypertensive disease, hemorrhagic stroke and atrial fibrillation. For ischemic heart disease (IHD) and ischemic stroke (cardiovascular diseases, CVD), the relationship is complex. Chronic heavy alcohol use has been associated with adverse cardiovascular outcomes. But light to moderate drinking seems to be related to reduced risk of ischemic diseases.

It is not well understood to what extent frequent episodes of heavy alcohol consumption may counteract the beneficial effect on heart disease and by which mechanisms episodes of heavy alcohol have a negative effect on heart disease. Even rare and occasional episodes of binge drinking seem to increase the risk in a recent study from the northernmost part of Norway. One would expect the protective effect to be more pronounced in individuals who do not binge drink, and not present in individuals who report substantial binge drinking. A recent meta-analysis on binge drinking including only 4718 IHD events gave some support for this notion. Our study will add to this by 6500 CVD cases.

Norwegian studies on adolescent and adult abstainers have shown higher risk of psychosocial factors and might suggest a J-shaped pattern. A general finding is that abstainers tend to have worse health and are poorer. One interpretation of this and similar findings is that since alcohol is such an important token in social interaction, abstainers are likely to differ as a social group and have a wide range of individual characteristics that could put them at increased risk of several health problems. Those who have moderate intake have in studies been shown to have higher cognitive ability compared to abstainers and that heavy drinkers have lower cognitive ability.

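### The fixed confounder list omits the self-reported health that all CONOR surveys collected, so some non-cardiometabolic ill health may stay unadjusted in the RQ 1–3 Cox models; a second model in CONOR would show how much it matters

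*Protocol*

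**What the plan says.** Three parts of the Protocol bear on this.

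- **The rival explanation.** Background and status of knowledge: "A general finding is that abstainers tend to have worse health and are poorer". Approaches, hypothesis and choice of method, on the raised risk in the lowest groups (underweight and abstainers): "Reverse causality by unmeasured health problems may explain this pattern in these groups". The remedy offered there is the family instrument: "Alcohol consumption in family members can be used similarly as instrument for own consumption to avoid the problem of sick quitters". (That section labels the instrument RQ 3; Research questions and Data analysis label it RQ 4, the number used here.)
- **The data held.** Data sources, on CONOR: "All the surveys included self-reported health and selected diseases, various risk factors, socio-demographic factors, use of medications". On the twin registry (NTR) questionnaires: "These questionnaires included detailed reports on health and risk factors". No NTR health item is named.
- **The adjustment set.** Statistical methods, Data analysis, lists age, smoking, physical activity and then: "self-reported disease (CVD, diabetes, antihypertensive medication) and psychosocial distress at baseline will be adjusted for as potential confounders". General self-reported health is not in the list, nor is any disease outside the cardiometabolic group.

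**The concern.** The Protocol raises ill health among abstainers as a possible non-causal source of the J-shape. It holds a health measure in every CONOR survey, but its fixed list uses only part of the health information. The people affected have no CVD, diabetes or antihypertensive treatment and are in poor health for some other reason, which may also be why they drink little or nothing. Under Main variables the lowest CONOR category is never/seldom, and the items shown do not separate former from lifelong abstainers. A health covariate is therefore one of the few ways to probe this bias inside the conventional models.

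At stake is how a lower CVD hazard in moderate drinkers than in never/seldom drinkers is read. If residual ill health is more common among never/seldom drinkers and raises CVD risk, part of an apparent protective effect is confounding, which a large sample does not reduce.

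**Working it through.** **Text comparison.** The claim concerns a covariate list, so there is no Protocol figure to reproduce.

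| Health information | Held, per Data sources | In the confounder list |
|---|---|---|
| Self-reported CVD, diabetes, antihypertensive medication | CONOR: selected diseases and medication use (the three items not named) | Yes |
| Psychosocial distress | CONOR mental health index (Main variables) | Yes |
| Self-reported health | All CONOR surveys; no NTR item named | No |

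The omission is confirmed for CONOR. For NTR, which RQ 1 pools with CONOR (47,848 + 8,028 = 55,876), the Protocol does not show whether a comparable item exists.

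**Illustration of size.** For a binary confounder, the factor by which the moderate versus never/seldom hazard ratio is distorted is approximately

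b = [1 + p_mod × (HR − 1)] / [1 + p_abs × (HR − 1)],

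and the hazard ratio after adjustment is the observed one divided by b.

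Inputs:
- Observed value 0.75: the planning relative risk for average consumption under Sample size and power. It serves only as an anchor.
- p_mod = 20% and p_abs = 25%, 30% or 40%: prevalence of poor self-reported health in moderate and never/seldom drinkers, **given the covariates already listed**. Assumed.
- HR = 1.3, 1.5 or 2.0: CVD hazard ratio for poor health, given the same covariates. Assumed.

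| HR | p_abs | b | 0.75 / b |
|---|---|---|---|
| 1.3 | 25% | 1.06 / 1.075 = 0.986 | 0.76 |
| 1.3 | 40% | 1.06 / 1.12 = 0.946 | 0.79 |
| 1.5 | 30% | 1.10 / 1.15 = 0.957 | 0.78 |
| 1.5 | 40% | 1.10 / 1.20 = 0.917 | 0.82 |
| 2.0 | 30% | 1.20 / 1.30 = 0.923 | 0.81 |
| 2.0 | 40% | 1.20 / 1.40 = 0.857 | 0.875 |

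The range is 0.76–0.88. If p_abs = p_mod, then b = 1 and nothing moves.

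**Could it explain the whole effect?** Moving 0.75 to 1.00 needs b = 0.75, that is p_abs = [(1 + 0.20 × (HR − 1)) / 0.75 − 1] / (HR − 1):
- HR 1.5: (1.10 / 0.75 − 1) / 0.5 = 93%
- HR 2.0: (1.20 / 0.75 − 1) / 1.0 = 60%
- HR 3.0: (1.40 / 0.75 − 1) / 2.0 = 43%

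At the assumed hazard ratios of 1.5 and 2.0 the required prevalence lies well above the assumed 25–40%. At HR 3.0, outside the assumed range, it would still be slightly above 40%.

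**The case against.** The case against is substantial, and much of it stands.

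- **No contradiction in the text.** A reader might infer that the Protocol attributes the abstainer excess to unmeasured health while holding the measure. The wording does not support this: it says such problems *may* explain the pattern, and it speaks of what is not measured. Holding one health item does not conflict with that.
- **Sick quitters are addressed.** The family instrument is proposed for this purpose. That stands as a description of the plan, but it is a separate analysis and leaves the RQ 1–3 hazard ratios as they are. A reader might also infer that a confounded conventional estimate spoils the RQ 4 comparison. That is weak: testing the conventional result is what the instrument is for, and failure to reproduce it would be informative.
- **Much of the pathway is already covered.** CVD, diabetes, antihypertensive medication, smoking, activity and distress are adjusted for. RQ 1 looks separately at pre-existing CVD, and RQ 2–3 examine distress, cognition and socioeconomic factors. Only the remainder is at issue, and whole-group prevalences of poor health would overstate it.
- **Adjustment is not purely bias removal.** Health is reported at the same survey as drinking over the past year. It may be partly a consequence of drinking, or of early CVD, so conditioning on it can remove real effect. Leaving it out of the main model is defensible.
- **No reference group is fixed.** The Protocol does not name never/seldom as the reference, and RQ 1 also concerns combinations with binge drinking and an interaction. The illustration says nothing about the interaction.

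What survives is narrow. The Protocol states its confounder list, the list leaves out a covariate already collected in CONOR, and that covariate bears on a bias the Protocol itself raises.

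**Conclusion.** The point holds as a low-cost improvement, not as an error that invalidates the analysis. Some non-cardiometabolic ill health may stay unadjusted in the RQ 1–3 Cox models, although CONOR holds a measure of it.

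Its size cannot be known from the documents. On the assumed inputs, a hazard ratio of 0.75 would become about 0.76–0.88. With no residual imbalance it would stay at 0.75. Both the prevalences and the hazard ratio for poor health are assumptions, and they must be read as conditional on the listed adjusters.

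Two stronger conclusions are tempting. One is that a removable share of sick-quitter bias has been shown to remain; the documents show only that it could. The other is that the health-adjusted estimate should become the main one. Because the temporal order of health and drinking at baseline is unclear, that would exchange one possible bias for another.

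**What to change.** In Statistical methods, Data analysis, pre-specify for RQ 1–3 a second Cox model in CONOR that adds baseline self-reported health to the listed confounders. Do the same in NTR only if a comparable item is identified and named; otherwise say that the comparison is confined to CONOR. Fit both models in the same participants, so that a change in the hazard ratio is not due to missing health data. Report the alcohol hazard ratios with and without the covariate, and state that any protective effect relative to never/seldom drinkers will be interpreted in light of both.

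The cost is one more model per question with a covariate already collected in CONOR, and some checking of the NTR questionnaires. The downside is possible over-adjustment, since self-reported health may partly follow from drinking or early CVD. The second model should therefore stand beside the main model and not replace it.
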